# Combining constraint-induced movement therapy and action-observation training in children with unilateral cerebral palsy: a randomized controlled trial

**DOI:** 10.1186/s12887-018-1228-2

**Published:** 2018-07-31

**Keywords:** Unilateral cerebral palsy, Upper extremity, Neuroimaging, Intensive therapy, Brain injuries, Treatment outcome

## Abstract

**Background:**

Upper limb (UL) deficits in children with unilateral cerebral palsy (uCP) have traditionally been targeted with motor execution treatment models, such as modified Constraint-Induced Movement Therapy (mCIMT). However, new approaches based on a neurophysiological model such as Action-Observation Training (AOT) may provide new opportunities for enhanced motor learning. The aim of this study is to describe a randomised controlled trial (RCT) protocol investigating the effects of an intensive treatment model, combining mCIMT and AOT compared to mCIMT alone on UL function in children with uCP. Additionally, the role of neurological factors as potential biomarkers of treatment response will be analysed.

**Methods:**

An evaluator-blinded RCT will be conducted in 42 children aged between 6 and 12 years. Before randomization, children will be stratified according to their House Functional Classification Scale, age and type of corticospinal tract wiring. A 2-week day-camp will be set up in which children receive intensive mCIMT therapy for 6 hours a day on 9 out of 11 consecutive days (54 h) including AOT or control condition (15 h). During AOT, these children watch video sequences showing goal-directed actions and subsequently execute the observed actions with the more impaired UL. The control group performs the same actions after watching computer games without human motion. The primary outcome measure will be the Assisting Hand Assessment. Secondary outcomes comprise clinical assessments across body function, activity and participation level of the International Classification of Function, Disability and Health. Furthermore, to quantitatively evaluate UL movement patterns, a three-dimensional motion analysis will be conducted. UL function will be assessed at baseline, immediately before and after intervention and at 6 months follow up. Brain imaging comprising structural and functional connectivity measures as well as Transcranial Magnetic Stimulation (TMS) to evaluate corticospinal tract wiring will be acquired before the intervention.

**Discussion:**

This paper describes the methodology of an RCT with two main objectives: (1) to evaluate the added value of AOT to mCIMT on UL outcome in children with uCP and (2) to investigate the role of neurological factors as potential biomarkers of treatment response.

**Trial registration:**

NCT03256357 registered on 21st August 2017 (retrospectively registered).

**Electronic supplementary material:**

The online version of this article (10.1186/s12887-018-1228-2) contains supplementary material, which is available to authorized users.

## Background

Cerebral palsy (CP) is the most common physical disability in childhood, occurring in 1–3 per 1000 live births [1]. Unilateral CP (uCP) accounts for 38% of the cases [2]. These children present with motor and sensory impairments predominantly on one side of the body, which are usually more pronounced in the upper limb (UL) [3]. These sensorimotor impairments typically lead to limited capability to perform daily tasks, having an impact on their participation and quality of life [4]. Hence, over the last decade, research into UL interventions for children with uCP has grown exponentially. One of the most popular treatment modalities amongst clinicians and researchers is modified Constraint-Induced Movement Therapy (mCIMT) [5]. mCIMT constrains the less impaired hand and targets intensive unimanual task-related practice with the more impaired UL. Despite increasing evidence proving the effectiveness of mCIMT in children with uCP, variable treatment outcomes have been reported [5–7].

The main focus of mCIMT is motor execution, although it has been shown that children with uCP also present with deficits in motor representations involved in the planning of movements [8]. Treatment modalities targeting motor representations might therefore further enhance the learning and rehabilitation process. Based on neurophysiological findings, it has been suggested that the use of systematic observations of meaningful actions followed by their execution, i.e. action-observation training (AOT), may accelerate the process of motor learning [9, 10]. Brain areas responsible for this action observation–action execution matching system are known as the mirror neuron system and include a bilateral network within the frontal premotor, parietal and temporo-occipital cortex underlying action observation [11]. Three recent studies using AOT in children with uCP have shown promising results [12–14]. However, it remains unclear whether combining mCIMT with a treatment modality targeting motor representation, such as AOT, will augment the treatment effects and result in longer retention.

Several studies investigating the efficacy of mCIMT in children with uCP, have reported a large inter-individual variability in treatment response [6, 15–17]. These studies have suggested that children with poorer UL function at baseline may benefit more from mCIMT. Moreover, some studies have investigated whether neurological factors, e.g. corticospinal tract (CST) wiring pattern or brain lesion characteristics, may determine treatment response. Despite the increasing number of studies investigating this research question, results are still contradicting. Two studies hypothesized that in children with an ipsilateral wiring pattern, constraining the less impaired UL may drive down primary motor cortex activity controlling both ULs, and thus possibly preventing improvement of the more impaired UL [18, 19]. In contrast, Islam et al. reported improved UL function after mCIMT irrespective of the CST wiring patterns [20], highlighting the importance of considering other relevant neurological factors. Interestingly, a few studies have already investigated the potential role of structural and functional connectivity in predicting treatment response, reporting that especially children with more affected structural and functional connectivity improved after mCIMT [21–23]. Notwithstanding the valuable insights reported by these studies, their sample sizes were relatively small. Moreover, the combination of structural and functional connectivity with CST wiring pattern to predict treatment outcome in children with uCP has not yet been investigated.

Furthermore, UL function has thus far mostly been evaluated using clinical scales on body function and activity level according to the International Classification of Functioning, Disability and Health (ICF) model. Whilst these clinical scales have been proven valid and reliable, they lack the information on anatomical motions at the single joint level. Moreover, they do not capture the complexity of UL motion, involving the coordinated interaction of movement sequences of multiple degrees of freedom. Hence, a more quantitative assessment, such as three-dimensional movement analysis (3DMA), may provide a better understanding of the changes that occur at the joint level and thus contribute to further insights on the effectiveness of UL treatment programs in children with uCP.

This study protocol describes the set-up for a single blind randomized controlled trial (RCT) comparing the effects of mCIMT with or without AOT on UL function using both clinical and kinematic outcomes. The first objective is to examine whether combining mCIMT with AOT will augment the treatment effects and result in longer retention. Secondly, the potential role of the anatomical characterization of the brain lesion, structural and functional connectivity and the CST wiring in predicting treatment response will be investigated. These findings might aid in guiding patient selection for tailor-made intervention programs in children with uCP.

### Hypothesis

The RCT will address the following research hypotheses:mCIMT, in combination with AOT, augments the treatment effects immediately after intervention and results in improved UL function with longer retention beyond mCIMT alone.The combination of neurological predictors, i.e. neuroanatomical brain lesion characteristics, structural and functional connectivity and CST wiring pattern, better determines treatment response compared to clinical predictors.Children with a bilateral and ipsilateral CST wiring respond less to the treatment compared to children with contralateral CST wiring in both intervention groups.In children with more lesions or disturbed connectivity in the areas involving the mirror neuron system, AOT is not as effective as in those with less lesions in this area.

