## Methods

### Study design

An evaluator-blinded RCT will be implemented comparing mCIMT with and without AOT on UL function in children with uCP. Ethical approval was obtained by the Ethical Committee of the University Hospitals Leuven (S56513). Before entering the study, written informed consent from all parents or care givers and verbal assent from all the participants will be obtained. Assessments will be performed at T0 (baseline, 3–4 month before the intervention onset), T1 (within 4 days before the intervention), T2 (within 4 days after the intervention) and T3 (6 months after the intervention). A summary of the experimental design is described in Fig. 1 and an overview of the outcome measures are presented in Table 1.

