### Sample size

Sample size estimate is based on the primary endpoint, which is defined as the immediate effect of the intervention on the primary outcome measure, i.e. bimanual performance measured with the Assisting Hand Assessment (AHA). The smallest detectable difference has been reported to be 5 AHA units [24]. A previous intervention study of intensive therapy in children with uCP [6], reported a standard deviation of 5.5 AHA units, which would translate into an effect size of 0.9. With this effect size, an alpha-level of 0.05, and a statistical power of 0.80, a sample size of 21 children is needed in each group to detect a difference equal to or larger than the smallest detectable difference of 5 AHA units between groups [24, 25]. Sample size estimates were calculated with G*Power [26, 27].

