### Statistical analysis

Descriptive statistics of the outcome variables will be reported by using means and standard deviations or median and interquartile ranges, depending on their data distribution. Normality will be checked with the Shapiro-Wilk test and histograms will be checked for symmetry. Mixed models will be used to study changes after the intervention over time. By using random effects, these models are able to correct for the dependency among repeated observations. Furthermore, these models deal with missing data offering valid inferences, assuming that missing observations are unrelated to unobserved outcomes [70]. Based on the data distribution, linear (parametric) or generalized (non-parametric) linear mixed models will be used. Changes over time will be tested between groups, by analysing treatment-time interactions. In case of such a significant treatment-time interaction, changes over time will be investigated separately in each group. Significant time trends will be further investigated with pairwise post hoc tests to compare time points. Additionally, the effect size will be calculated using the Cohen’s d formula (small, 0.2–0.5; medium, 0.5–0.8, and large > 0.8) [71]. Both clinical (age, baseline AHA score, sensory function, mirror movements) and neurological predictors (brain lesion characteristics, structural and functional connectivity and CST wiring) will be included as covariates in the models for the primary outcome measure, together with their interaction with time and treatment to evaluate their potential confounding factor. The two-sided 5% level of significance will be used. All statistical analyses will be performed using SAS version 9.2 (SAS Institute, Inc., Cary, NC) and SPSS Statistics for Windows version 24.0 (IBM Corp. Armonk, NY: IBM Corp.).

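### Retention is claimed between arms and as duration, but the single 6-month visit shows only what remains, and the stated follow-up tests give no between-arm estimate of it

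*Protocol article*

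**What the plan says.** The first objective, at the end of the Background, is to "examine whether combining mCIMT with AOT will augment the treatment effects and result in longer retention". Hypothesis 1 repeats this: the combination augments the immediate effect and "results in improved UL function with longer retention beyond mCIMT alone". Retention is therefore claimed alongside the immediate effect, and as a comparison between arms.

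Under Study design, the assessments from the end of the camp onward are "T2 (within 4 days after the intervention) and T3 (6 months after the intervention"; Table 1 shows no later or intermediate visit. AHA is measured at T0, T1, T2 and T3.

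Under Sample size, the primary endpoint is "defined as the immediate effect of the intervention on the primary outcome measure". Retention is not part of it.

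Statistical analysis gives three steps in order: "Changes over time will be tested between groups, by analysing treatment-time interactions"; then "In case of such a significant treatment-time interaction, changes over time will be investigated separately in each group"; then "Significant time trends will be further investigated with pairwise post hoc tests to compare time points". It does not define retention and names no pair of time points.

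**The concern.** There are two difficulties.

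First, one visit after T2 fixes the level at 6 months. It cannot separate a gain that lasts longer from a gain that was larger to begin with, so the wording goes beyond the design.

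Second, the claim compares arms, but every step described after the overall interaction works inside one arm. The interaction covers all visits together and does not isolate what is left at T3. A reader who wants to know about retention may then compare the T2-T3 test in one arm with the same test in the other. That contrasts two significance statements and does not estimate a difference. It also leans in one direction: the arm that gained more has more units to lose, so its fall is easier to detect even when it keeps the same share and is still ahead. A non-significant fall in the other arm may be taken as retention when power was simply low.

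At stake is the retention half of hypothesis 1. AOT gains could be reported as fading while mCIMT gains hold, in a trial where AOT children are still better off at 6 months.

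**Working it through.** **The plan's own figure.** Sample size section: difference 5 AHA units, SD 5.5, effect size 5/5.5 ≈ 0.9, two-sided alpha 0.05, power 0.80. A two-sample t-test with the noncentral t gives n = 20.39, rounded up to 21 per arm, with power 0.812 at 21. The stated figure reproduces.

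**Assumptions not in the protocol.** T1-T2 gains of 10 (AOT) and 5 (mCIMT), chosen to differ by the plan's 5 units; the share of gain kept at T3; and SD 5.5 for each change score. The protocol takes 5.5 from a previous intervention study for the immediate effect, not for T2-T3 change.

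**Between-arm contrasts.** With the same share r kept in both arms and gains 5 units apart:

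- T2-T3 contrast (AOT minus control) = −(1 − r) × 5
- T1-T3 contrast = r × 5

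| Share kept | T2-T3 | T1-T3 |
|---|---|---|
| 25% | −3.75 | +1.25 |
| 50% | −2.5 | +2.5 |
| 75% | −1.25 | +3.75 |
| 100% | 0 | +5 |

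The control gain cancels out. Below full retention the two contrasts have opposite signs. With control keeping 50%, the T2-T3 contrast favours AOT only if 10 × (1 − r) < 2.5, that is if AOT keeps more than 75%. At 70% against 50%, AOT loses 3.0 and control 2.5, yet AOT leads by 7.0 − 2.5 = 4.5 at T3.

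**Within-arm T2-T3 tests.** Paired t-test, n = 21, 20 degrees of freedom, noncentrality = loss/SD × √21. At SD 5.5:

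- loss 2.5: 2.5/5.5 × 4.583 = 2.08, power 0.51
- loss 5: 5/5.5 × 4.583 = 4.17, power 0.98

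The arms are independent, so P(significant fall in AOT only) = power(AOT) × [1 − power(control)]. At 50% kept this is 0.977 × (1 − 0.509) = 0.48. The reverse is 0.509 × (1 − 0.977) = 0.01.

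| Gains, share kept, SD | True AOT lead at T3 | Fall in AOT only | Fall in control only |
|---|---|---|---|
| 10 and 5, 50% both, 5.5 | 2.5 | 48% | 1% |
| 10 and 5, 75% both, 5.5 | 3.75 | 42% | 8% |
| 8 and 3, 50% both, 5.5 | 2.5 | 69% | 2-3% |
| 10 and 5, 50% both, 4 | 2.5 | 22% | 0% |
| 10 and 5, 75% vs 50%, 5.5 | 5 | 25% | 25% |

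**Effect of the interaction gate.** The within-arm steps follow only a significant interaction. With four visits and independent equal-variance residuals, the first scenario passes the gate in about 83% of trials, and a fall in AOT only then appears in about 42% of all trials. Among the trials that pass, that is 0.42/0.83 ≈ 51%, so the gate does not filter the pattern out. The further requirement of a significant time trend within an arm was not modelled.

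**The T1-T3 tests from the same set.** In the first scenario the retained gains are 5 and 2.5, so the powers are again 0.98 and 0.51: a significant gain in AOT only appears in 48% and in control only in 1%. Among trials with the misleading T2-T3 pattern, the AOT gain from T1 to T3 is also significant in 98%. In the 75% vs 50% scenario the T1-T3 tests favour AOT in 49% of trials and control in about none.

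**Power for a between-arm T1-T3 contrast of 2.5 units**, 21 per arm: 0.51 at SD 4, 0.30 at SD 5.5, 0.20 at SD 7.

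**The case against.** The strongest reply is that the protocol nowhere says retention will be read from T2-T3, nor that a non-significant fall will count as retention. The pairwise tests name no pair and so include T1-T3, which points the right way in the scenarios checked. This stands. A reader might infer that the plan commits the trial to a wrong-way retention verdict, but the text does not support that. Such a verdict would require reporting T2-T3 and disregarding T1-T3.

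It can also be said that the treatment-time interaction is already a between-group test and that T3 enters it, so the needed contrast is a component of the planned model. That is correct, and it is why the remedy is cheap. But the overall test does not report that component, and a within-arm T1-T3 test does not estimate a difference from mCIMT alone.

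The hypothesis may be read loosely as better maintained at 6 months, which T3 can address. That reading is fair; the wording should then say so.

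Finally, naming a secondary contrast is often left to the full protocol or analysis plan, neither of which is shown. An unnamed contrast alone would not be a finding. What remains is stated text: a claim of duration that no analysis plan can rescue without more visits, and a sequence that turns to within-arm tests to support a between-arm claim.

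**Conclusion.** The point holds in a limited form. The design supports a statement about the benefit remaining at 6 months, not about how long it lasts, and the described sequence yields no between-arm estimate of that benefit. Reading retention from within-arm T2-T3 tests is permitted but not prescribed. If it were done, a fall in the AOT arm only would appear in about 48% of trials in the main scenario (about 42% of all trials after the interaction gate, 22% without the gate at SD 4) while AOT is 2.5 units ahead at T3. These figures rest on assumed gains, kept shares and SD of change; with full retention in both arms there is no penalty. The immediate-effect primary endpoint and its sample size are untouched. This is a worthwhile, inexpensive improvement and not a flaw in the main comparison.

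**What to change.** - In the Background objective and in hypothesis 1, replace the retention wording by a larger AHA gain still present 6 months after the intervention, and make no statement on duration.
- In Statistical analysis, assess this by the between-arm difference in AHA change from T1 to T3, with a 95% CI, from the mixed model already planned, as a secondary contrast after the immediate effect.
- State that within-arm T2-T3 comparisons are descriptive and that a non-significant fall is not evidence of retention.

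The cost is a rewording and one further contrast, with no new data or visits. The claim becomes narrower, limited to the level at 6 months. Power for a 2.5-unit difference at T3 is only about 0.3 at SD 5.5, so the interval should carry the interpretation and a non-significant result should not be read as no benefit.

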## Methods

### Study design

An evaluator-blinded RCT will be implemented comparing mCIMT with and without AOT on UL function in children with uCP. Ethical approval was obtained by the Ethical Committee of the University Hospitals Leuven (S56513). Before entering the study, written informed consent from all parents or care givers and verbal assent from all the participants will be obtained. Assessments will be performed at T0 (baseline, 3–4 month before the intervention onset), T1 (within 4 days before the intervention), T2 (within 4 days after the intervention) and T3 (6 months after the intervention). A summary of the experimental design is described in Fig. 1 and an overview of the outcome measures are presented in Table 1.

**Fig 1 Fig1:**
[figure not shown]
Flow-chart of the described RCT following the CONSORT guidelines. Abbreviations: uCP, unilateral cerebral palsy; CST, corticospinal tract; mCIMT, modified constraint-induced movement therapy; AOT, Action-Observation Training

**Table 1 Tab1:** Overview of the assessments at each time-point

		Baseline (T0)	Pre-evaluation (T1)	Post-evaluation (T2)	Follow-up evaluation (T3)
Descriptive characteristics			MACS HFC CVI Sensory assessment Mirror Movements		
Outcome measures	Body Function and Structure	pROM, muscle strength, grip force and spasticity	pROM, muscle strength, grip force and spasticity	pROM, muscle strength, grip force and spasticity	pROM, muscle strength, grip force and spasticity
	Activity	AHA, MA2, JTHFT, ABILHAND-Kids, CHEQ	AHA, MA2, JTHFT, ABILHAND-Kids, CHEQ and Tyneside Pegboards	AHA, MA2, JTHFT, ABILHAND-Kids, CHEQ and Tyneside Pegboards	AHA, MA2, JTHFT, ABILHAND-Kids, CHEQ and Tyneside Pegboards
	Participation		CPQOL and Life-H		CPQOL and Life-H
	Motion analysis		3DMA	3DMA	3DMA
Neurological predictors		sMRI, dMRI and rsfMRI	TMS		

*Abbreviations*: *MACS* Manual Ability Classification System, *HFC* House Functional Classification, *CVI* Cerebral Visual Impairment, *pROM* passive range of motion, *AHA* Assisting Hand Assessment, *MA2* Melbourne Assessment 2, *JTHFT* Jebsen-Taylor Hand Function Test, *CHEQ* Child Hand-use Experience Questionnaire, *CPQOL* CP quality of life questionnaire, *Life-H* Life Habits questionnaire, *3DMA* three-dimensional motion analysis, *sMRI* structural MRI, *dMRI* diffusion MRI, *rsfMRI* resting-state functional MRI, *TMS* transcranial magnetic stimulation

### Study sample and recruitment

Children with spastic uCP will be recruited via the CP-care program of the University Hospitals Leuven. They will be selected upon the following inclusion criteria: (1) confirmed diagnosis of uCP; (2) aged 6–12 years at time of baseline assessment; (3) sufficient cooperation to comprehend and complete the test procedure and cooperate in the camp activities; (4) minimal ability to actively grasp and stabilize an object with the more impaired hand (House Functional Classification Score ≥ 4). Children will be excluded in case of previous UL surgery in the last 2 years, or botulinum toxin-A injections 6 months prior to the baseline assessment.

